#### Qualitative data

The six-stage thematic analysis approach will be employed to analyse all interviews, as suggested by Braun and Clarke.^29^ This involves becoming familiar with the data, generating initial codes, searching for themes, reviewing themes, defining and naming themes and subthemes, and producing the report. We will adhere to the four criteria for trustworthiness established by Lincoln and Guba: credibility, dependability, confirmability and transferability.^30^ Each step of the qualitative data collection and analysis will be guided by a qualitative research expert. The qualitative data will be managed and analysed using NVivo V.12.

#### Progression criteria

This feasibility study will be overseen and governed by the Trial Steering Committee (TSC), which will include the chief investigator, principal investigator, two lay members, topic experts in TBI and one paramedic. The role of the TSC is to provide external oversight and to ensure that the study is conducted in compliance with Good Clinical Practice guidelines.^31 32^

The traffic light approach (green/amber/red), also known as a (stop–amend–go) rule, will be used to determine whether or not to proceed with a full definitive trial.^33^ Green (go) indicates that the study meets the preset criteria, and that it would be feasible for a full-powered definitive trial to be conducted without any modifications to the study protocol. Amber (amend) indicates that further feasibility work or modifications to the protocol are required before proceeding with the full trial. Red (stop) indicates that proceeding to a definitive study is not recommended. Taking into account the feasibility outcomes, as well as qualitative interviews with patients and paramedics, a decision will be made regarding whether or not to proceed with the trial or whether to make any amendments to the study design. The progression criteria are shown in table 2.

**Table 2 T2:** Progression criteria to proceed with a definitive trial

	Contributing data	Green (proceed to a definitive trial)	Amber (proceed to a definitive trial following some changes to the protocol)	Do not proceed to a definitive trial
Screening	Training and delegation logs	At least 20 paramedics at participating ambulance hubs trained and on delegation logs	At least 10 paramedics at participating ambulance hubs trained and on delegation logs	Less than 10 paramedics at participating ambulance hubs trained and on delegation logs
Recruitment acceptability	Screening & recruitment log	≥80% of eligible screened patients are consented to take part	≥60% of eligible screened patients are consented to take part	<60% of eligible screened patients are consented to take part
Retention	Screening & recruitment log	Retention of ≥90% of study participants until study completion	Retention of ≥80% of study participants until study completion	Retention of <80% of study participants until study completion
Study procedures	Participation data	At least 85% of the outcome data are collected (eg, case report forms)	A minimum of 60% of the outcome data are collected (eg, case report forms)	<60% of the outcome data are collected (eg, case report forms)
Adverse events	Participation data	No or very minor adverse events and no participants discontinued the study	Minor or serious adverse events leading to 10% or less participants discontinuing the study	Serious adverse events leading to >10% of participants discontinuing the study
Acceptability	Participant interview Paramedics questionnaire and interviews	Responses to OADRI all ‘agree’ or ‘strongly agree’. No major barriers to acceptability/participation identified during interviews with paramedics and patients	Responses to OADRI mainly ‘agree’ or ‘strongly agree’. Some barriers to participation identified during interviews but remediable action identified	Responses to OADRI mainly ‘disagree’ or ‘strongly disagree’. Major barriers to acceptability/participation identified during interviews with no clear remediable action

OADRI, Ottawa Acceptability of Decision Rules Instrument.

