### Study duration and sample size

This is a feasibility study, in which evaluating recruitment rate is an outcome; therefore, it is not possible to specify a sample size a priori. However, we intend to recruit participants for a fixed period of 6 months. Based on data routinely collected by the Manchester University NHS Foundation Trust, a total of 5332 patients arrived in the ED by ambulance with a primary complaint of head injury over a period of 4 years and 9 months up to November 2020. We intend to recruit participants from two similarly sized MTCs. We anticipate that approximately 1100 patients will be eligible to participate in this study during the recruitment period. Accounting for the availability of trained paramedics on the study delegation log and concurrent injuries to other body systems that would exclude patients from participating in this study, approximately 100 participants can be recruited to this study. This number of participants is generally accepted as being appropriate for studies that focus on assessing feasibility and acceptability.^20^

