### Outcomes

We will study the following feasibility outcomes:

The number of eligible patients who are approached.The proportion of those approached who consent to participate in the study.The completeness of data collection.The completeness of follow-up.The number and proportion of patients with neurosurgically significant TBI.Determination of the interobserver reliability of the CCHR completed by prehospital care providers and ED physicians.Determination of the interobserver reliability for each component of the CCHR assessed by prehospital care providers and ED physicians.The diagnostic performance and clinical sensibility of the CCHR in the opinion of attending paramedics.Determination of the acceptability of trial processes as perceived by paramedics and patients.

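### Table 2 sets no threshold for the number or rate of patients recruited, so the progression rule can read green when very few patients have been recruited

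*Protocol article*

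**What the plan says.** **Recruitment as an outcome.** Protocol article, Study duration and sample size, names recruitment rate as an outcome and gives this as the reason for fixing no sample size. It sets the duration ("we intend to recruit participants for a fixed period of 6 months") and a forecast ("approximately 100 participants can be recruited to this study"). Data analysis, Quantitative data, adds that enrolment per week will be reported.

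**The progression rule.** Under Progression criteria, green means that the preset criteria are met and that a definitive trial is feasible with the protocol unmodified. Table 2 has six rows: paramedics trained and on delegation logs, consent, retention, outcome data collected, adverse events, and acceptability. The consent row is green at "≥80% of eligible screened patients are consented to take part", amber from 60% and red below 60%. The row labelled Screening counts paramedics, not patients. The text before the table says that the feasibility outcomes and the interviews will be taken into account in the decision.

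**The consent outcome.** The Outcomes section defines it on another base: "The proportion of those approached who consent to participate in the study".

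**The patient pool.** Study duration and sample size states "We anticipate that approximately 1100 patients will be eligible to participate in this study during the recruitment period". Its next sentence then allows for paramedic availability and for injuries to other body systems before arriving at about 100.

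**The concern.** The study exists partly to learn whether enough patients can be recruited for a large diagnostic accuracy study. That quantity is forecast and reported, but it is not tested in the table that decides whether to proceed. The consent row conditions on patients who have already reached the screening log. The sample is a convenience sample and the logs are completed by attending paramedics, so an eligible patient who is never logged does not enter the denominator. The other rows are percentages, a count of paramedics or qualitative judgements, and none of them would register a shortfall in patients.

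At stake is a wrong go decision: the table could support launching an expensive multicentre study, without modification, after recruitment far below forecast. A smaller matter is that the consent proportion has two denominators in the article and the base figure of 1100 carries a misleading label. Both make the recruitment results harder to interpret.

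**Working it through.** **1. Reproducing the article's own figure.** Inputs from Study duration and sample size: 5332 ambulance head-injury arrivals at one trust over 4 years 9 months (57 months), two similarly sized centres, 6 months.

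- Per month, one centre: 5332 / 57 = 93.5
- Six months, one centre: 93.5 × 6 = 561
- Six months, two centres: 561.3 × 2 = 1123

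This agrees with the stated 1100 to about 2%. No deduction for GCS, age or other injuries is needed to reach it, so the 1100 is a count of arrivals with a head-injury complaint. The step from 1100 to about 100 cannot be derived, because the article gives no fraction for paramedic availability or for exclusions.

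**2. The forecast as a rate.** 100 participants / 26 weeks = 3.8 per week.

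**3. What the consent row returns.** The counts below are illustrative assumptions. Row value = consented / eligible screened.

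| Eligible screened | Consented | Row value | Colour | Per week (÷ 26) | Share of forecast 100 |
|---|---|---|---|---|---|
| 12 | 10 | 83% | green | 0.4 | 10% |
| 30 | 25 | 83% | green | 1.0 | 25% |
| 125 | 100 | 80% | green | 3.8 | 100% |

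The row cannot separate a tenth of the forecast from the whole of it.

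**4. Direction of the denominator mismatch.** Patients approached for consent are taken to be a subset of those eligible and screened, so consented / screened cannot exceed consented / approached. With an illustrative 200 screened, 120 approached and 100 consented:

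- Table 2 base: 100 / 200 = 50%
- Outcomes base: 100 / 120 = 83%

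Table 2 uses the stricter base. The mismatch therefore cannot turn a poor result green.

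**5. Where a volume threshold could sit.** If the true expected count is 100 and the count is Poisson (an assumption):

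- P(fewer than 100) = 0.49
- P(fewer than 80) = 0.017, about 2%

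A green mark at 100 would be missed about half the time by a study recruiting exactly as forecast. A mark at 80 would be missed about 2% of the time.

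**The case against.** The strongest reply is that low recruitment would not go unseen. Progression criteria says that the feasibility outcomes inform the decision. Those outcomes include the number of eligible patients approached, and weekly enrolment is reported. The Screening row tests paramedic capacity, which is one of the two constraints named in the sample size section. An all-green table also needs high retention, high data completeness and uniformly favourable OADRI responses, so passing the consent row alone does not make the study green. All of this stands, and it softens the consequence. It does not remove the gap: weighing an outcome without a threshold is what a preset traffic-light rule is meant to avoid, and none of the other rows depends on how many patients were recruited.

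Three stronger readings are tempting, and the document does not support them.

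- *The two consent denominators cause a false green.* Table 2 uses the larger base and so the lower percentage.
- *The same data can be two colours.* Only Table 2 carries colours. The proportion in the Outcomes list is descriptive and has no cut-off.
- *About 91% of eligible patients will be missed* (1 − 100/1100). The 1100 is not an eligible count, and part of the drop to 100 is due to exclusions. The capture rate among truly eligible patients cannot be derived from the article.

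**Conclusion.** The point holds in a limited form. Table 2 has no criterion on the number or rate of patients recruited, although the article names recruitment rate as an outcome and forecasts about 100 in 6 months. As printed, the consent row is green at 10 of 12 or 25 of 30, which is 10% or 25% of the forecast, and no other row would detect the shortfall. That the table lacks the criterion is a matter of reading it. The size rests on illustrative counts and on the article's own forecast, and it does not predict that recruitment will fail. Decision makers may still weigh low volume informally.

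The consent wording and the label on the 1100 are points of clarity. Neither changes a Table 2 threshold.

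**What to change.** 1. **Add a recruitment-volume row to Table 2**, fixed before accrual is reviewed and anchored on the forecast of about 100 in 6 months with an allowance below it. One example is green at 80 or more consented participants with CCHR data, amber 60–79, red below 60. These cut-offs apply the consent row's own 80% and 60% steps to 100. They are a suggestion, and the steering committee may prefer an equivalent weekly rate (80 / 26 = 3.1 and 60 / 26 = 2.3 per week).
2. **Use one consent denominator for the progression decision.** Keep eligible screened patients, as in Table 2, and report consent among those approached alongside it, with both terms defined.
3. **Relabel the 1100** as expected head-injury ambulance arrivals at the two centres, before exclusions.

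The cost is one table row and some wording, with no new data collection and no effect on participants or their care. The article reports that recruitment is already under way, so the row should be recorded as a dated change made without reference to accrual. The downside is that green becomes harder to reach.

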### Evaluation of acceptability

We will use a qualitative approach to evaluate the acceptability of trial processes used to study participants. We will purposively sample (a) study participants and (b) paramedics. The intention is to maximise heterogeneity (according to age, sex and ethnic origin, and for paramedics, seniority and base ambulance station). Patients and participating paramedics will be interviewed for the purpose of exploring their experiences of participating in a study of this nature. Previous emergency care research has demonstrated the value of this method in providing information regarding the feasibility and design of a larger study.^21^

To maximise convenience for participants and thereby recruitment, participants will be invited to take part in a semistructured interview either by telephone, face-to-face or video conference. Informed consent will be obtained from all participants. We will explore the factors that facilitate or discourage participation in the research. Paramedics and study participants will be offered a £30 high street voucher to thank them for taking part. Telephone and sign language interpreters will be provided where necessary. The interview topic guides (online supplemental appendix 1) consist of a number of questions and prompts concerning the patients and paramedics’ experiences of participating in this study, as well as the paramedics’ perceptions of the viability of the CCHR. Prior to commencement of the interviews, two pilot interviews will be carried out. To determine the relevance, clarity and duration required to complete each interview, one will be with a paramedic and the other will be with a patient.^22^

10.1136/bmjopen-2023-077191.supp1Supplementary data

The Ottawa Acceptability of Decision Rules Instrument (OADRI) is a 12-item instrument that will be used to measure paramedics’ attitudes toward the CCHR and clinical sensibility.^23^ Paramedics will be asked to provide their level of agreement with 12 statements about the CCHR using a 6-point Likert scale. The first seven statements are worded in such a way that a higher number indicates higher acceptance, while the last five are worded in the opposite manner to minimise the acquiescence bias.^24^

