### Data analysis

#### Quantitative data

A descriptive analysis will be conducted based on the baseline data for patients enrolled in the study to characterise the demographic and clinical profile. This will include the number of eligible participants who were approached, the proportion who consented to participate, data completeness (expressed as number and percentage) for each variable collected and number and percentage of participants completing follow-up. We will also report recruitment data as rates (number of participants enrolled per week across the study period).

The interobserver reliability between paramedics and emergency physicians’ use of the CCHR will be calculated using Cohen’s kappa, a statistical method for measuring agreement between two observers, together with 95% CIs. Additionally, we will report upon the CCHR’s diagnostic performance for ruling out clinically significant TBI. This will be achieved by calculating the sensitivity, specificity, positive and negative likelihood ratios with 95% CIs against a reference standard of traumatic intracranial lesion, which will be identified from in-hospital records. Given the nature of this feasibility study, the analyses will be viewed as exploratory, preliminary and will be descriptive in nature. Furthermore, to determine the acceptability of the CCHR, the OADRI average item scores will be calculated, with higher scores indicating greater acceptability.

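### Table 2 grades OADRI acceptability by raw agreement although five of the 12 items are worded against the rule, so full acceptance reaches at most amber

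*Protocol article*

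**What the plan says.** Three places in the Protocol article bear on this.

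- **Evaluation of acceptability** describes the instrument. "The Ottawa Acceptability of Decision Rules Instrument (OADRI) is a 12-item instrument", and paramedics give their "level of agreement with 12 statements about the CCHR using a 6-point Likert scale". Seven items run in the accepting direction: "The first seven statements are worded in such a way that a higher number indicates higher acceptance". The remaining items do not, and the article gives the reason for this: "while the last five are worded in the opposite manner to minimise the acquiescence bias".
- **Data analysis, Quantitative data** says that "the OADRI average item scores will be calculated, with higher scores indicating greater acceptability". It does not mention reversing any item.
- **Progression criteria, Table 2, Acceptability row** sets the grades. Green is "Responses to OADRI all ‘agree’ or ‘strongly agree" together with "No major barriers to acceptability/participation identified during interviews with paramedics and patients". Amber is "Responses to OADRI mainly ‘agree’ or ‘strongly agree", with some barriers at interview that can be remedied. Red is responses mainly in the two disagree categories, with major barriers and no clear remedy. None of the three grades separates the first seven items from the last five.

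**The concern.** Agreeing with a statement worded against the decision rule expresses non-acceptance. A grade that counts agreement with all 12 statements as favourable therefore reads five of them backwards. The description of the instrument and the decision rule cannot both stand as written.

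The table is a preset go/amend/stop rule, and green is meant to signal that a definitive study could proceed without protocol changes. If the rule is applied literally, unanimous acceptance by paramedics leads to a call for amendments. The response pattern that satisfies the OADRI part of green is indiscriminate agreement, which is what the opposed wording is there to guard against. If the committee instead chooses a reading once the responses are in, the criterion is no longer preset. Paramedics' attitudes to the rule are a stated objective, and the OADRI is the only quantitative measure in this row.

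**Working it through.** **Inputs.** From Evaluation of acceptability: 12 items, 7 favourable and 5 opposed, on a 6-point agreement scale. From Table 2: green needs all responses to be agree or strongly agree, amber needs mainly these, and red needs mainly disagree or strongly disagree.

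**Assumptions.** The article does not define mainly; I take it as more than half. Full acceptance means agreeing with all seven favourable items and disagreeing with all five opposed ones. Full rejection is the mirror image. No numeric coding of the scale is needed.

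**Step 1: Table 2 read literally.** The count is the number of responses in the two agree categories.

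| Pattern | Favourable items | Opposed items | Raw agreement | OADRI grade |
|---|---|---|---|---|
| Full acceptance | 7 of 7 | 0 of 5 | 7/12 = 58% | amber |
| Full rejection | 0 of 7 | 5 of 5 | 5/12 = 42% (7/12 disagree) | red |
| Agrees with everything | 7 of 7 | 5 of 5 | 12/12 = 100% | green component met |
| Disagrees with everything | 0 of 7 | 0 of 5 | 0/12 = 0% | red |

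Full acceptance fails the word all on five items. A single fully accepting paramedic is enough to remove green for the group.

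**Step 2: the amber/red boundary.** Let p be the share of items answered in the accepting direction, taken as the same in both item sets, with only agree or disagree answers used. Raw agreement is [7p + 5(1 − p)]/12 = (5 + 2p)/12. This runs from 5/12 = 42% at p = 0 to 7/12 = 58% at p = 1. It passes one half where 5 + 2p = 6, that is at p = 0.5. For such respondents the line between mainly agree and mainly disagree still falls in the right place, but total acceptance and total rejection differ by only 2 responses in 12. The boundary is poorly resolved rather than reversed. The outright error is at green.

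**Step 3: the same rule after reversing items 8 to 12.** The count is now of responses in the accepting direction.

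| Pattern | Accepting direction | OADRI grade |
|---|---|---|
| Full acceptance | 12/12 | green component met |
| Full rejection | 0/12 | red |
| Agrees with everything | 7/12 | amber |
| Disagrees with everything | 5/12 | red |

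Reversal alone puts full acceptance in green and takes blanket agreement out of it.

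**The case against.** The strongest reply is that reversal is already understood. The article explains which items are opposed and why, and its statement that a higher average means greater acceptability holds only if those items are reversed. Table 2 could then be shorthand for accepting-direction responses, with the scoring step left to a fuller document. This stands for the average score: silence on reverse scoring in the analysis section is not in itself a fault. It does not rescue Table 2, which is a decision rule fixed in this article, speaks of responses rather than scores, and conflicts with the instrument as described in the same article.

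It is also fair to say that the consequences are limited. Progression rests on all the feasibility outcomes and the interviews, and this questionnaire is part of one row of six.

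A reader might infer more than the text supports:

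- **That blanket agreement turns the row green.** It does not. Green in the same cell also requires no major barriers at interview. That condition is additional, so equally it cannot restore green to genuine acceptance.
- **That the plan will average unreversed items.** The stated meaning of the average rules this out as the intention, so figures for an unreversed mean would describe an analysis the authors do not plan.
- **That true acceptance would stop the programme, or rejection pass it.** Uniform acceptance lands in amber and uniform rejection in red.
- **That requiring all responses to be favourable is itself an error.** A strict green with mainly as amber is coherent. How often it would fail depends on the number of questionnaire respondents, which the article does not give (its figure of 20 concerns trained and delegated paramedics), and on correlation between one person's answers. That is a separate matter of preference.

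**Conclusion.** Wrong as written, moderate severity. On a literal reading, full acceptance gives 7 of 12 raw agreements (58%) and reaches at most amber. The only pattern that meets the OADRI component of green is agreement with every item, including the five opposed ones. The green result follows from the stated item directions and the word all, and needs no assumption about scale coding. The amber and red placements also rest on reading mainly as more than half. Severity stays moderate because the error lies mainly at the green/amber boundary of one of six progression rows, in an observational feasibility study that leaves patient care unchanged.

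**What to change.** Either of two edits is enough.

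1. In Quantitative data, state that items 8 to 12 are reverse-scored before the average is taken and before Table 2 is applied. In Table 2, say that all three grades refer to the reverse-scored responses.
2. Reword all three grades by item direction. Green and amber would refer to agreement with items 1 to 7 and disagreement with items 8 to 12, and red to the opposite.

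The words all and mainly can stay; no new cut-offs are needed. The cost is one sentence and a small edit to one table row, with no new data and no change to the questionnaire. The article describes the study as still recruiting in April 2024, so what matters is that the wording is settled before any OADRI responses are graded.
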